### Outcome measures

Primary outcome is the number of obstetric complications throughout the first year after the intervention. Obstetric complications will be defined as the number of neonates with perinatal asphyxia (Apgar score 5-minutes <7 and/or arterial umbilical pH < 7.05, hypoxic ischemic encephalopathy (HIE), number of newborns with damage caused by shoulder dystocia (e.g. lesion of brachial plexus, clavicle fracture), number of women with eclampsia, number of women with severe post partum haemorrhage (blood transfusion >4 packed cells, embolisation, hysterectomy). Shoulder dystocia is hereby described as every additional manoeuvre for successful alleviation.

Sub analysis will be performed to identify possible changes in subgroups. These groups concern term infants (gestation over 37 weeks), singleton pregnancies and cephalic presentation at birth.

Secondary outcomes are perinatal and maternal mortality, divided by causes of death.

These complications will be obtained from the regular obstetric recordings after informed consent from the participating hospitals (with exception of damage due to shoulder dystocia and severe postpartum haemorrhage, these data will be registered separately). Before the start of the project indicators will be developed to evaluate patient safety, teamwork and human factors. These indicators will be registered in a subgroup of the participating hospitals. This group will consist of 100 obstetric complications equally distributed in the intervention and control group.

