## Methods/Design

The proposed research concerns a multicentre randomised controlled trial of obstetric departments in the Netherlands. These obstetric departments will be randomly assigned to receive multidisciplinary team training in a medical simulation centre or to a control arm without any team training.

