### Intervention

The intervention group will have multidisciplinary team training in a medical simulation centre. These team trainings are given by specially trained instructors and facilitators (gynaecologists, communication experts and psychologists). All instructors and facilitators are trained in crew resource management. To make the context of the training lifelike these take place in an entirely reconstructed delivery room. State of the art high fidelity patient simulators will be used. Fetal distress (including a cardiotocogram training program), postpartum haemorrhage, eclampsia, umbilical cord prolapse and shoulder dystocia scenario's are practiced on the birthing simulator Noelle™ (Gaumard Miami, Florida) and Prompt Birthing Trainer™ (Limbs & Things, Bristol), perimortem caesarean section on the emergency care simulator ECS™ (Meti, Sarasota, Florida), and resuscitation of asphyxiated infants on the neonatal simulator (Baby Hal™, Gaumard, Miami, Florida). For hospitals randomised to receive the team training, the interventions will be planned. Depending on the size of the department it concerns 3 up to 10 sessions. A team will consist of a group of about 6 care workers in means of one gynaecologist and one or more residents, midwifes and nurses. For one hospital all sessions are carried out in a timeframe with a maximum of 4 weeks. This means that several teams of the same hospital will be trained. In the real life setting in their own hospitals there will be a different composition of team members but every delivery room care worker has been trained in the simulation centre.

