The team training will take place at the medical education and simulation centre in Eindhoven (medsim) where the following scenarios will be trained: Fetal distress including CTG analysis, shoulder dystocia, severe postpartum haemorrhage, eclampsia, umbilical cord prolapse and perimortem caesarean section. The scenarios are based on national and international accepted guidelines by NVOG (The Dutch Society for Obstetrics and Gynaecology) and MOET (Managing Obstetric Emergencies & Trauma). Each scenario starts with a briefing session in a simulated emergency room of 10 minutes in which the case is presented by means of a video play on a wide screen. The team will then move to the simulated delivery room. In the delivery room they have to treat the patient. The patient is a an advanced interactive birthing simulator. The facilitator gives wireless instructions to the robot from the control room. The whole session is videotaped. The simulation session will take 20 minutes. Then the team will move to the briefing room. The facilitators will give feedback on teamwork and skills using video recording. The debriefing session will take about 30 minutes.

There will be an effect measurement after six months following the team training, by in-situ training in all participating hospitals, including the control arm.

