### Statistics

#### Sample size

The composite measure of poor perinatal and maternal outcome in the non training group was thought to be 15%, on the basis of data obtained from the National Dutch Perinatal Registry and the guidelines of the Dutch Society of Obstetrics and Gynaecology (NVOG). We anticipated that multidisciplinary team training would reduce this risk to 5%. A sample size of 24 centres with a cluster size of each at least 200 deliveries, each 12 centres per group, was needed for 80% power and a 5% type 1 error probability (two-sided). We assumed an Intraclass Correlation Coefficient (ICC) value with a maximum of 0.08. Because there is an uncertainty about the complication rate and perhaps this is lower than expected a sample size of 1000 deliveries per hospital was taken. In conclusion we will try to randomise 24 obstetric departments in the Netherlands with an one year follow-up.

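### Newborn injury counts only if caused by shoulder dystocia, which is described by a staff action trained in one arm only, so whether the same injury counts can depend on allocation

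*Protocol article*

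**What the plan says.** Under Outcome measures, one component of the primary outcome is the "number of newborns with damage caused by shoulder dystocia (e.g. lesion of brachial plexus, clavicle fracture"). The same paragraph describes the qualifying condition: "Shoulder dystocia is hereby described as every additional manoeuvre for successful alleviation". No other primary component uses the term, so the sentence serves to define this one.

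The Intervention section makes dystocia part of the training: "umbilical cord prolapse and shoulder dystocia scenario's are practiced on the birthing simulator". It adds that "The facilitators will give feedback on teamwork and skills using video recording" and that, in intervention hospitals, "every delivery room care worker has been trained in the simulation centre". Under Methods/Design, the alternative allocation is "or to a control arm without any team training".

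On data sources, Outcome measures says complications come from the regular obstetric recordings, "with exception of damage due to shoulder dystocia and severe postpartum haemorrhage, these data will be registered separately". The injury item is thus described as dystocia damage already at the point of registration.

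**The concern.** An outcome definition should classify the same infant in the same way in either arm. Here an injury must first be attributed to shoulder dystocia, and dystocia is described by an additional manoeuvre, which is an act of the care team and not a state of mother or child. The intervention trains teams in handling that situation; the control arm receives no team training. The condition for counting an injury therefore lies downstream of the allocation.

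If training changes how often dystocia is recognised or how often a manoeuvre is used, the proportion of injuries that qualify changes too, even when the number of injured infants does not. The observed contrast then mixes a real effect on injury with a change in classification. The mixture passes into the primary composite and into the cost per prevented complication planned under Cost analysis. A later analysis plan could not recover injuries that were never registered because they did not qualify.

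**Working it through.** **1. The plan's own figure.** Inputs from Sample size: 15% versus 5%, ICC 0.08, 200 deliveries per centre, 80% power, two-sided 5%.
- Individual-level size (pooled variance, no continuity correction): 141 per arm.
- Design effect: 1 + (200 − 1) × 0.08 = 16.92.
- Centres per arm: 141 × 16.92 / 200 = 11.93, so 12 per arm and 24 in total; power with 12 per arm is 80.5%.

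The stated 24 centres reproduce. This point does not change that figure.

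**2. Injury component.** Let s be the share of newborn injuries attributed to dystocia, and so counted. Then

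observed RR = true RR × s(training) / s(control).

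The article gives no value for s, so these are assumptions:

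| s control | s training | ratio | true RR | observed RR |
|---|---|---|---|---|
| 60% | 60% | 1.00 | 0.80 | 0.80 |
| 60% | 70% | 1.17 | 0.80 | 0.93 |
| 60% | 80% | 1.33 | 0.80 | 1.07 |
| 60% | 80% | 1.33 | 0.70 | 0.93 |
| 60% | 80% | 1.33 | 1.00 | 1.33 |
| 80% | 60% | 0.75 | 1.00 | 0.75 |

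The last row reverses the direction: with no true effect, the component would then show a false benefit.

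**3. Whole composite.** Let w be the share of counted control-arm events that are injuries, assumed to be 5–20%. Suppose every component truly falls by 20% and the ratio is 1.33:

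composite RR = 0.80 × (1 − w) + 0.80 × w × 1.33.
- w = 5%: 0.760 + 0.053 = 0.81.
- w = 20%: 0.640 + 0.213 = 0.85.

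**4. On the planning rates.** Take a trained-arm composite of 5.0%, with injuries making up 5–20% of it.
- Ratio 1.33: 5.0% × (1 + w/3) = 5.08–5.33%.
- Ratio 1.5 (60% versus 90%): 5.0% × (1 + w/2) = 5.1–5.5%; power at 12 centres of 200 per arm falls from 80.5% to 79.3–75.4%.

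Steps 3 and 4 treat injuries as separate events. If some injured infants also count through asphyxia and each infant is counted once, the shift is smaller.

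**The case against.** The strongest reply is that limiting the component to the trained mechanism is a legitimate choice: it gains specificity, and injuries unrelated to dystocia could only add noise. The scenarios are also said to follow accepted national and international guidelines, so control staff may know the same manoeuvres, and a threshold of any additional manoeuvre is low. Both leave room for little difference between arms. The in-situ session at six months, held in all hospitals including controls, might narrow it further.

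Much of this stands as a limit on size. It does not make the definition independent of allocation. The six-month session comes halfway through the outcome year and its content is not described.

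Three stronger readings should be resisted.
- A reader might infer that an injury is excluded unless a manoeuvre was written down. The text speaks of the manoeuvre, not of its documentation, and separate registration might start from the injured infant.
- A reader might infer that staff aware of the allocation decide what is entered. The article does not say who completes the registration or whether events are reviewed. Such detail commonly sits in the full protocol, so its absence is no finding.
- A reader might infer that injuries are certain to be counted more often in trained hospitals. The article does not list the manoeuvres taught and says nothing on direction.

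**Conclusion.** The point holds as one about the definition of a single primary-outcome component. The article ties the injury count to a staff action, trains that situation in one arm only, and states nothing that makes classification the same in both arms.

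More counting in trained hospitals is the more plausible direction; it would understate a benefit, not create one. That is inference, and the opposite direction would also be bias. For the injury component the distortion can be large: under the assumed shares of 60% versus 70–80%, a true 20% reduction appears as 0.93–1.07. A reader might take this to mean that the primary composite could reverse. The figures do not support that: with injuries at 5–20% of events, 0.80 moves only to about 0.81–0.85. All the shares are assumptions, since the article supplies none.

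**What to change.** Reword the component so that, in both arms, it counts every newborn brachial plexus lesion, every clavicle fracture and any other birth injury type the trial lists in advance, whether or not dystocia or a manoeuvre was noted. Listing types in advance matters because the present wording gives examples only. Take the diagnosis from the neonatal examination or discharge diagnosis, entered in the separate registration already planned. With s = 1 in both arms, the observed ratio equals the true one.

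Keep the dystocia-attributed count as a sensitivity analysis, and report the frequency of dystocia as a process measure.

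The cost is a reworded component and registration form. Some injuries not due to dystocia will be included, which slightly dilutes the component. Randomisation should balance them on average, provided newborns are examined in the same way in both arms.

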### Economic evaluation

The trial results will be incorporated in a cost-effectiveness analysis to compare the costs and effects of multidisciplinary team training in a medical simulation centre (experimental strategy) versus no such training (reference strategy).

#### Cost analysis

The process of care is distinguished into two cost stages: delivery/childbirth and postnatal stage and three cost categories: direct medical costs (all costs in the health care sector), direct non-medical costs (costs outside the health care sector that are affected by health status or health care) and indirect costs of the pregnant woman and her partner (costs of sick leave). For each stage and each cost category, costs are measured as the volumes of resources used multiplied with appropriate valuations (cost-per-unit estimates, fees, national reference prices). Costs during childbirth are dominated by the course of childbirth and type of delivery. Cost volumes in the postnatal stage consist of maternal care (hospitalisation etc.), neonatal care (admission to NICU/neonatology ward, outpatient visits) and primary care. If neonatal health at discharge is suboptimal, further direct medical, direct non-medical and indirect costs may occur. Hence, for these infants, resource use of infants and/or parents is measured during 12 months after childbirth. Volumes of health care resource use are measured prospectively alongside the clinical study in all participating centres as part of the case report form (CRF). Health resource use outside the hospital is recorded by questionnaires. Valuations of direct medical resources are estimated as cost per unit estimates comprising (true economic) costs, i.e. including shares of fixed costs and hospital overheads. Cost per units are estimated for at least one teaching and one non-teaching hospital. An analysis based on reimbursement fees is added. Direct medical volumes outside the hospital and direct non-medical volumes are valued using national reference prices. Indirect costs are quantified but remain unvalued. Study-specific costs are excluded from analysis.

The costs of the implementation intervention will be calculated separately. We will calculate the costs of patient counselling, the costs of education of health care professional as well as the costs of distribution of patient leaflets. The sensitivity of costs and health outcomes for various parameters is tested in sensitivity analysis and visualised in Incremental Cost-Effectiveness Ratio (ICER) graphs and acceptability curves. When the study would show that multidisciplinary team training would be effective, the primary economic analysis will be a cost-effectiveness analysis. If multidisciplinary team training would appear to reduce complications, we will calculate the costs per prevented complication. No power calculations will be performed for the economic evaluation study as it is embedded in a randomised controlled trial.

### Statistics

#### Sample size

The composite measure of poor perinatal and maternal outcome in the non training group was thought to be 15%, on the basis of data obtained from the National Dutch Perinatal Registry and the guidelines of the Dutch Society of Obstetrics and Gynaecology (NVOG). We anticipated that multidisciplinary team training would reduce this risk to 5%. A sample size of 24 centres with a cluster size of each at least 200 deliveries, each 12 centres per group, was needed for 80% power and a 5% type 1 error probability (two-sided). We assumed an Intraclass Correlation Coefficient (ICC) value with a maximum of 0.08. Because there is an uncertainty about the complication rate and perhaps this is lower than expected a sample size of 1000 deliveries per hospital was taken. In conclusion we will try to randomise 24 obstetric departments in the Netherlands with an one year follow-up.

#### Data analysis

Our primary (base-case analyses) will be performed according to the intention-to-treat principle and stratified for teaching or non-teaching hospital. A baseline analysis will be performed to examine the comparability of groups at baseline for both costs and outcomes. To investigate whether data are normally distributed a Kolmogorov-Smirnov test will be performed. Despite the usual skewness in the distribution of costs, the arithmetic means will be generally considered the most appropriate measures to describe cost data. Therefore arithmetic means (and standard deviations) will be presented. In case of skewness of the cost data, non-parametric bootstrapping will be used to test for statistical differences in costs between the intervention and control group. Non-parametric bootstrapping is a method based on random sampling with replacement based on individual data of the participants. The bootstrap replications will be used to calculate 95% confidence intervals around the costs (95% CI), based on the 2.5th and 97.5th percentiles. If cost data are distributed normally, t-tests will be used. The Incremental Cost-Effectiveness Ratio (ICER) will be determined on the basis of incremental costs and effects of team training compared with non-team training. The cost-effectiveness ratio will be stated in terms of costs per outcome rate, the cost-utility ratio will focus on the net cost per QALY (Quality Adjusted Life Year) gained. The robustness of the ICER will be checked by non-parametric bootstrapping (1000 times). Bootstrap simulations will also be conducted in order to quantify the uncertainty around the ICER, yielding information about the joint distribution of cost and effect differences. The bootstrapped cost-effectiveness ratios will be subsequently plotted in a cost-effectiveness plane, in which the vertical line reflects the difference in costs and the horizontal line reflects the difference in effectiveness. The choice of treatment depends on the maximum amount of money that society is prepared to pay for a gain in effectiveness, which is called the ceiling ratio. Therefore, the bootstrapped ICERs will also be depicted in a cost-effectiveness acceptability curve showing the probability that team training is cost-effective using a range of ceiling ratios.

Sensitivity analysis will be performed for the most important variables, i.e. costs, number of complications etcetera. In a scenario analysis we will evaluate what the effect is of variation of the frequency of team training, in a range of once every two years versus once in three months.

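### The only stated use of hospital baseline outcomes is a comparability check; the analysis is valid, but adding the baseline rate as a covariate could recover unused precision

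*Protocol article*

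**What the plan says.** The Data analysis section says that the primary analysis will be "performed according to the intention-to-treat principle and stratified for teaching or non-teaching hospital". It then gives baseline data one role: "A baseline analysis will be performed to examine the comparability of groups at baseline for both costs and outcomes". It names no baseline covariate and no effect model for the clinical primary outcome; most of the section concerns costs and the cost-effectiveness ratio.

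On where the outcome data come from, Outcome measures says: "These complications will be obtained from the regular obstetric recordings". It excepts shoulder dystocia damage and severe postpartum haemorrhage, which are registered separately.

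The abstract makes the centre the unit of analysis. The Sample size section plans for a control risk of 15% ("The composite measure of poor perinatal and maternal outcome in the non training group was thought to be 15" per cent) and an intervention risk of 5% ("We anticipated that multidisciplinary team training would reduce this risk to 5" per cent). It gives the design as "A sample size of 24 centres with a cluster size of each at least 200 deliveries, each 12 centres per group", and the ICC as follows: "We assumed an Intraclass Correlation Coefficient (ICC) value with a maximum of 0.08". It then raises the cluster size to 1,000 deliveries per hospital, in case the complication rate is lower than expected.

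**The concern.** In a trial of 24 hospitals, the precision of the treatment effect is governed by how much hospitals differ from one another. A hospital's own earlier complication rate is a natural candidate for explaining part of that difference, and the plan already intends to examine outcomes at baseline. Looking at comparability does not by itself make the effect estimate more precise. The article also states no consequence if the check shows an imbalance. Any decision to adjust taken at that point would depend on the data.

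What is at stake is efficiency. The plan's own safeguard against a low complication rate is more deliveries per hospital, and that hardly touches the between-hospital part of the error. Without recruiting more hospitals, explaining between-hospital variance is the main lever left.

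**Working it through.** **Inputs from the article.** Control risk 15%, intervention risk 5%, 12 hospitals per arm, 200 deliveries per hospital raised to 1,000, ICC at most 0.08, two-sided 5% type 1 error, 80% power (Sample size).

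**Assumptions, not in the article.** The correlation r between a hospital's baseline and follow-up rates, taken as 0.3 to 0.8. ICC values below 0.08. An illustrative intervention risk of 7.5%, which applies to 15% the roughly 50% reduction that the Background cites from a British cohort.

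**1. The plan's own figure.** The usual two-proportion formula for 15% against 5% gives 141 per arm. The design effect at 200 deliveries is 1 + 199 × 0.08 = 16.92. Then 141 × 16.92 = 2,386 deliveries per arm, and 2,386 / 200 = 11.93, so 12 hospitals per arm. The stated 24 centres reproduce.

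**2. What more deliveries buy.** At 12 hospitals per arm, power for 15% against 5% is 80.5% with 200 deliveries and 82.2% with 1,000 (normal approximation), or 77.7% and 79.4% with a t distribution on 22 df.

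**3. Between-hospital share of the variance of a hospital's rate.** The share is ICC / (ICC + (1 − ICC)/m), with m deliveries.

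- ICC 0.08, m = 200: 0.08 / (0.08 + 0.0046) = 94.6%
- ICC 0.08, m = 1,000: 0.08 / (0.08 + 0.00092) = 98.9%
- ICC 0.02, m = 1,000: 0.02 / (0.02 + 0.00098) = 95.3%
- ICC 0.01, m = 1,000: 91.0%
- ICC 0.001, m = 1,000: 50.0%

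These shares concern hospital rates. For individual outcomes the between-hospital share is the ICC itself, so 8% at most.

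**4. Chance difference between arms.** At a 15% rate and ICC 0.08, the between-hospital SD is √(0.08 × 0.15 × 0.85) = 0.101. The SD of the difference between two means of 12 hospitals is 0.101 × √(2/12) = 0.041, or 4.1 points. At ICC 0.02 the same steps give 0.0505 × √(2/12) = 0.021, or 2.1 points.

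**5. Effect of adjustment on power.** The between-hospital variance is multiplied by 1 − r². The variance of the treatment effect is then [p₁(1 − p₁) + p₂(1 − p₂)] × [ICC(1 − r²) + (1 − ICC)/m] / 12. Power comes from the noncentral t distribution, with 22 df unadjusted and 21 df adjusted. For 15% against 7.5%, the first bracket is 0.1275 + 0.0694 = 0.1969. With m = 1,000:

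| ICC | r | Second bracket | Standard error | Effect / SE | Power |
|---|---|---|---|---|---|
| 0.08 | none | 0.0809 | 0.0364 | 2.06 | 50% |
| 0.08 | 0.3 | 0.0737 | 0.0348 | 2.16 | 54% |
| 0.08 | 0.5 | 0.0609 | 0.0316 | 2.37 | 62% |
| 0.08 | 0.7 | 0.0417 | 0.0262 | 2.87 | 78% |
| 0.08 | 0.8 | 0.0297 | 0.0221 | 3.40 | 90% |
| 0.04 | none | 0.0410 | 0.0259 | 2.89 | 79% |
| 0.02 | none | 0.0210 | 0.0186 | 4.04 | 97% |

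**The case against.** A reader might infer that the plan has decided against a baseline covariate. The article does not support that. It names no effect model for the clinical outcome and excludes no covariate, and a covariate list is commonly left to a full protocol or analysis plan, neither of which is shown. What can be said is that a comparability check is the only use stated.

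A reader might also infer that chance imbalance between 12 and 12 hospitals biases the result and needs correcting. It does not. Stratified randomisation followed by a matching stratified intention-to-treat analysis is valid, and the ICC in the sample size already allows for this chance variation. The 24 centres reproduce, so the sample size is not in error on this account.

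The size of the gain is open to challenge, and most of that challenge stands. The ICC of 0.08 is a ceiling, and at 0.02 there is almost no power left to gain in the 7.5% scenario. The article gives no correlation, and r = 0.3 adds only 4 points. For the planned 15% to 5%, unadjusted t-based power is already about 79%.

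The baseline itself may be incomplete. Two components are registered separately, so the full composite may not exist before randomisation, and a partial baseline would probably correlate less well with the follow-up composite. Extending the adjustment to costs is also tempting, because the comparability check mentions costs. However, the Cost analysis section describes resource use measured prospectively alongside the study, so baseline costs may not exist.

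None of this removes the suggestion. It rests on the sponsor's own planning ICC and on a baseline outcome that the plan already means to examine.

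**Conclusion.** The point holds as a recommendation on efficiency. The stated analysis is valid but may use the baseline information less well than it could. The claim that variation is nearly all between hospitals is right only for the variance of hospital rates: about 99% at ICC 0.08 and 95% at ICC 0.02, with 1,000 deliveries each. At ICC 0.08 the potential gain for 15% against 7.5% runs from 4 to 40 percentage points of power over r = 0.3 to 0.8. It shrinks quickly as the ICC falls, since unadjusted power is 79% at ICC 0.04 and 97% at ICC 0.02. The correlations, the lower ICC values and the 7.5% risk are assumptions, so the gain is a range that cannot be fixed from the article.

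**What to change.** State that the primary effect analysis includes each hospital's pre-randomisation complication rate as a covariate alongside teaching status, and that it does so whatever the comparability check shows. Either a hospital-level analysis of covariance or a hospital-level term in a mixed model would serve. If shoulder dystocia damage and severe haemorrhage have no baseline record, use the baseline rate of the routinely recorded components and say so in advance. Keep the comparability table as description. No matching change is asked for in the cost analysis.

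The cost is one model term and one degree of freedom of about 22, plus extraction of the pre-randomisation records for the routine components where the planned baseline analysis does not already supply them. The number of hospitals does not change.

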**Methods/design:**

The aim of the present study is to evaluate the cost-effectiveness of multidisciplinary team training in a medical simulation centre in the Netherlands to reduce the number of medical errors in obstetric emergency situations. We plan a multicentre randomised study with the centre as unit of analysis. Obstetric departments will be randomly assigned to receive multidisciplinary team training in a medical simulation centre or to a control arm without any team training.

The composite measure of poor perinatal and maternal outcome in the non training group was thought to be 15%, on the basis of data obtained from the National Dutch Perinatal Registry and the guidelines of the Dutch Society of Obstetrics and Gynaecology (NVOG). We anticipated that multidisciplinary team training would reduce this risk to 5%. A sample size of 24 centres with a cluster size of each at least 200 deliveries, each 12 centres per group, was needed for 80% power and a 5% type 1 error probability (two-sided). We assumed an Intraclass Correlation Coefficient (ICC) value of maximum 0.08.

The analysis will be performed according to the intention-to-treat principle and stratified for teaching or non-teaching hospitals.

Primary outcome is the number of obstetric complications throughout the first year period after the intervention. If multidisciplinary team training appears to be effective a cost-effective analysis will be performed.

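### The cost comparison rests on a bootstrap of individual participants that ignores the hospital; the normality pre-test in front of it is uninformative, though it does little harm itself

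*Protocol article*

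**What the plan says.** The Data analysis section of the protocol article sets out the cost comparison in four steps.

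- A normality check: "To investigate whether data are normally distributed a Kolmogorov-Smirnov test will be performed".
- A target: "Despite the usual skewness in the distribution of costs, the arithmetic means will be generally considered the most appropriate measures".
- Two routes: "In case of skewness of the cost data, non-parametric bootstrapping will be used to test for statistical differences in costs", and "If cost data are distributed normally, t-tests will be used". The bootstrap 95% limits are "based on the 2.5th and 97.5th percentiles".
- A definition of the bootstrap: "random sampling with replacement based on individual data of the participants".

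The abstract (Methods/design) describes the trial differently: "We plan a multicentre randomised study with the centre as unit of analysis".

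The text does not say outright that the Kolmogorov-Smirnov p-value is the switch between the routes, but it names no other criterion. It gives no test level, no variant of the test (standard, or with Lilliefors critical values for an estimated mean and SD), and no unit for the normality test or the t-test.

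**The concern.** The section already expects skewed costs and already takes the arithmetic mean as its target. Testing raw costs for normality therefore asks a question the plan has answered. It is also not the relevant question: validity depends on the sampling distribution of the difference in means.

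The more serious matter is where the rule ends. Hospitals are randomised, yet the only bootstrap described draws individuals. If costs vary between hospitals at all, an interval built that way is too short. Cost-effectiveness is the stated aim of the study, so a cost difference could be declared on precision that the 24 randomised units do not provide.

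**Working it through.** **Inputs from the protocol article.** 24 centres, 12 per group; 200 deliveries per centre as the minimum and 1000 as the number taken, so 24 × 1000 = 24,000 births; 15% vs 5%; 80% power; two-sided 5%; ICC at most 0.08 (clinical outcome). **Assumed here, because the article gives no cost figures:** lognormal or normal costs, a cost ICC of 0 to 0.08, and a 5% level for the normality test.

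**1. The plan's own figure.** There is none for costs. The sample size reproduces: n per arm = [1.96√(2 × 0.10 × 0.90) + 0.8416√(0.15 × 0.85 + 0.05 × 0.95)]² / 0.10² = 140.1, so 141. Design effect = 1 + 199 × 0.08 = 16.92. 141 × 16.92 / 200 = 11.93, so 12 centres per arm (power 80.5%). The plan thus allows for clustering when sizing the trial, but not in the bootstrap it describes for costs.

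**2. Pre-test on 24,000 births.** Simulated rejection is 98-100% at skewness 0.15 and 100% from 0.30 upward. Only at skewness 0.06 does it fall, to 7% (standard) or 65% (Lilliefors). For realistic costs the t-test branch is never reached.

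**3. Pre-test on 24 hospital values.** The standard test rejects 0.2% at skewness 0.8, 2% at 1.75, 12% at 3.3 and 27% at 6.2. With Lilliefors critical values the figures are 14%, 42%, 69% and 87%.

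**4. Individual-level routes under no true difference** (24 × 1000 births, 400 trials per row, Monte Carlo SE about 1.1 points near 5%). Design effect = 1 + 999 × ICC; theoretical rejection = 2[1 − Φ(1.96/√DE)].

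| Cost ICC | DE | t-test, individuals | Bootstrap, individuals | Theory | t-test, hospital means |
|---|---|---|---|---|---|
| 0 | 1 | 6.3% | 6.8% | 5.0% | 6.3% |
| 0.01 | 10.99 | 52% | 54% | 55% | 5.0% |
| 0.08 | 80.92 | 84% | 85% | 83% | 4.8% |

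The two routes agree with each other, and both fail once hospitals differ. The hospital-mean t-test does not.

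**5. Hospital-level routes under no true difference** (12 vs 12, 6,000 trials per row, standard pre-test; CV = √(exp(σ²) − 1)).

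| Hospital values | t-test | Percentile bootstrap | Gated rule |
|---|---|---|---|
| Normal | 5.3% | 7.9% | 5.3% |
| Lognormal σ 0.25 (CV 0.25) | 4.8% | 7.8% | 4.8% |
| Lognormal σ 0.5 (CV 0.53) | 4.5% | 7.9% | 4.6% |
| Lognormal σ 1.0 (CV 1.31) | 3.4% | 9.0% | 5.8% |

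A further simulation put the percentile bootstrap at 7.5-9.6%. It put the gated rule at 4.5-5.5% up to CV 1.0 with the standard test, and at 5.0-6.6% up to CV 0.67 with Lilliefors values. The narrowness of the percentile limits follows from theory: √(11/12) × 1.96 / 2.074 = 0.905, about 10% narrower than t limits.

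**6. Plausible spread of hospital means.** CV of a hospital mean = birth-level CV × √(ICC + (1 − ICC)/1000). At ICC 0.08 the factor is √0.08092 = 0.284. A birth-level CV of 1.0 gives 0.28. Hospital-mean CVs of 1.0 and 1.5 would need birth-level CVs of about 3.5 and 5.3.

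**The case against.** The strongest reply is that the pre-test is harmless. At the individual level that the section describes, it always sends the analysis to the bootstrap, which amounts to one fixed method, and the t-test would have given the same answer. At hospital level the standard test seldom fires, so the rule is nearly always the t-test and holds about 5%. This stands. A reader might infer that the gate distorts the error rate, that the test cannot detect skew in 24 values, or that the two routes always have different error rates. The documents do not support these readings. The routes differ only if hospitals are resampled, which the section does not propose. Power at 24 values depends on the unstated variant of the test. The gated rule moves clearly above 5% only with Lilliefors values at hospital-mean CVs of 1.0-1.5 (7.9-9.3%), which step 6 makes implausible.

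A second reply is that little rests on a cost p-value. The economic analysis is conditional on effectiveness and has no power calculation, and the economic decision draws on the cost-effectiveness plane and acceptability curve. That limits the weight of the point. It does not justify reporting a 95% cost interval that ignores the randomised unit.

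A third is that participants, in a trial that randomises departments, might mean hospitals. The wording points to individuals. On the other reading the percentile limits on 12 per arm are still too narrow, as step 5 shows.

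**Conclusion.** The point holds in a limited form. The normality pre-test is uninformative and could go, but removing it alone would change almost nothing. The material fault is the cost comparison it leads to. Resampling individuals conflicts with the centre as unit of analysis and gives simulated false-positive rates of about 52-54% at a cost ICC of 0.01 and 84-85% at 0.08. Keeping the percentile method and changing only the unit would leave limits about 10% too narrow and a type I error of about 7.5-9.6%.

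These sizes rest on assumed cost distributions and an assumed cost ICC; the article's 0.08 is for the clinical outcome. With a cost ICC of zero the individual-level routes would be acceptable. A reader might extend the criticism to the primary clinical result. Nothing here supports that, and the sample size for that outcome reproduces with clustering included.

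**What to change.** Delete the Kolmogorov-Smirnov test and the two-branch rule. Pre-specify one analysis: the difference in arithmetic mean cost between arms, computed on hospital means, adjusted for teaching status, with a t-based 95% interval. A permutation test over hospitals is an optional check.

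This needs a change of wording and no new data. The price is a wider interval. Against a percentile bootstrap of hospitals it is about 10% wider (1/0.905 = 1.10). Against the individual-level interval it is wider by roughly √DE: √10.99 = 3.3 times at a cost ICC of 0.01 and √80.92 = 9.0 times at 0.08. That extra width is the between-hospital uncertainty that the present method leaves out.

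The change does not touch the bootstrap used for the cost-effectiveness plane and acceptability curve. The same definition of resampling is the only one given for those outputs, so their resampling unit should be stated when the section is revised.
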